# Study protocol for a prospective, multicenter, single-arm study investigating the impact of the implementation of standardized hyperkalemia management in chronic kidney disease patients

**DOI:** 10.1186/s12882-026-04801-8

**Published:** 2026-04-21

**Keywords:** Hyperkalemia, Renin-angiotensin-aldosterone system inhibitors, Quality improvement, Disease management, Guideline adherence, Chronic kidney disease

## Abstract

**Background:**

Hyperkalemia (serum potassium > 5.0 mmol/L) is a common and clinically significant complication in patients with chronic kidney disease (CKD), particularly among those treated with renin-angiotensin-aldosterone system inhibitors (RAASi). Although guideline-directed medical therapy recommends proactive hyperkalemia management to enable continued RAASi use, real-world practice remains suboptimal. Key challenges include inadequate potassium monitoring after RAASi initiation or dose escalation, unnecessary RAASi dose reduction or discontinuation following hyperkalemia episodes, and poor long-term treatment adherence. Moreover, evidence regarding the cardio-renal benefits of RAASi optimization supported by structured hyperkalemia management in Chinese CKD populations is limited. This study aims to bridge the gap between Kidney Disease: Improving Global Outcomes (KDIGO) and Chinese CKD guideline recommendations and routine clinical practice through a nationwide quality improvement program (QIP).

**Methods:**

This prospective, multicenter, single-arm study will enroll approximately 1,000 adult Chinese patients with non-dialysis CKD and hyperkalemia across 50 sites. The QIP includes comprehensive and reinforcement training for healthcare professionals (HCPs) based on the KDIGO 2024 guidelines, supported by regular quality audits and feedback. Patient-directed interventions comprise structured education delivered by HCPs and self-learning modules. Participants will receive standardized hyperkalemia management over 96 weeks, including protocolized serum potassium monitoring (every 3 months or monthly for high-risk patients), RAASi dose optimization, and long-term potassium control. The primary endpoint is the proportion of patients achieving RAASi optimization with normokalemia (3.5-5.0 mmol/L) at 48 weeks. Secondary endpoints include sustained potassium control, RAASi optimization over time, medication adherence, hyperkalemia recurrence and severity, cardiorenal outcomes, and safety endpoints.

**Discussion:**

As the first nationwide QIP focusing on hyperkalemia management in CKD patients in China, this study is expected to provide real-world evidence on the effectiveness of standardized hyperkalemia care in facilitating sustained RAASi use. By aligning clinical practice with guideline recommendations, the program has the potential to improve long-term cardio-renal outcomes and inform future CKD care strategies.

**Trial registration:**

ClinicalTrials.gov, NCT06884267; registered March 13, 2025.

**Supplementary Information:**

The online version contains supplementary material available at 10.1186/s12882-026-04801-8.

## Background

Hyperkalemia, defined as a serum potassium level > 5.0 mmol/L, is one of the most common and clinically significant electrolyte abnormalities encountered in clinical practice [1, 2]. The kidneys play a central role in maintaining potassium homeostasis through filtration, reabsorption, and secretion; consequently, disturbances in potassium balance are particularly prevalent in patients with chronic kidney disease (CKD) owing to reduced glomerular filtration rate and tubular dysfunction [3]. In addition, treatment with renin-angiotensin-aldosterone system inhibitors (RAASi), a cornerstone therapy in CKD, further increases the risk of hyperkalemia by inhibiting aldosterone-mediated renal potassium excretion [4]. The reported prevalence of hyperkalemia (> 5.0 mmol/L) among patients with CKD ranges from 8% to 38% [5]. In China, a large outpatient survey demonstrated that while 3.86% of the general outpatient population experienced hyperkalemia, the prevalence increased markedly to 22.89% among individuals with CKD [6]. Importantly, even mild-to-moderate elevations in serum potassium have been consistently associated with increased short- and long-term mortality, higher rates of cardiac arrhythmias, and adverse hospital outcomes in patients with CKD or cardiovascular disease [7, 8]. These risks are further amplified in patients with severe hyperkalemia or comorbid conditions such as advanced CKD or acute kidney injury, underscoring the need for vigilant potassium monitoring and proactive management strategies [8–10].

In patients with CKD, this risk of hyperkalemia frequently leads to conservative prescribing practices, including suboptimal dosing or premature discontinuation of RAASi therapy in routine clinical care [11–13]. However, extensive evidence demonstrates that RAASi therapy confers substantial clinical benefit, including reductions in blood pressure and proteinuria, slowing of estimated glomerular filtration rate (eGFR) decline, and significant decreases in the risks of kidney failure, cardiovascular morbidity, and all-cause mortality among patients with CKD [14]. Importantly, observational analyses have shown that RAASi discontinuation following hyperkalemia is associated with markedly increased risks of mortality, cardiovascular events, and progression to end-stage kidney disease (ESKD), underscoring the cardioprotective and renoprotective consequences of sustained RAASi exposure [15]. In recognition of these benefits, contemporary clinical guidelines emphasize that hyperkalemia should be actively managed to enable continuation of RAASi therapy whenever possible. The Kidney Disease: Improving Global Outcomes (KDIGO) 2024 guideline recommends a stepwise approach to hyperkalemia management in CKD, prioritizing correction of reversible factors, optimization of using potassium-lowering agents before considering dose reduction or discontinuation of RAASi or mineralocorticoid receptor antagonists as a last resort [16, 17].

Despite clear and consistent guideline recommendations, a substantial gap persists between evidence-based guidance and real-world hyperkalemia management in patients with CKD. In routine clinical practice, serum potassium monitoring remains insufficient, and adherence to long-term hyperkalemia management strategies is often suboptimal, limiting the ability to maintain guideline-recommended RAASi therapy [11–13]. Large-scale observational studies indicate that more than half of eligible CKD patients receive lower-than-recommended RAASi doses, while approximately 14–16% discontinue RAASi therapy altogether [11]. From the patient perspective, inadequate disease awareness, poor adherence to potassium monitoring schedules, and challenges in sustaining long-term treatment regimens represent key barriers. From the clinician perspective, concerns regarding hyperkalemia risk, variability in treatment approaches, and the absence of a unified, standardized management pathway frequently result in conservative RAASi prescribing, including dose reduction or discontinuation, even when alternative potassium-lowering strategies are available [11–13]. Moreover, although guideline-directed medical therapy emphasizes proactive hyperkalemia management to preserve RAASi exposure, robust real-world evidence demonstrating the long-term cardiovascular and renal benefits of sustained, guideline-based hyperkalemia care remains limited, particularly in the Chinese CKD population.

Therefore, this study was designed to evaluate the impact of implementing a standardized, guideline-directed hyperkalemia management strategy through a structured quality improvement program (QIP). By targeting both healthcare professionals (HCPs) and patients, the study aims to bridge the gap between guideline recommendations and routine clinical practice, improve serum potassium monitoring and control, facilitate RAASi optimization, and generate real-world evidence on the long-term cardiorenal benefits of consistent hyperkalemia management in patients with CKD.

## Methods/design

### Study design

This multicenter, prospective, single-arm study (ClinicalTrials.gov identifier: NCT06884267) is designed to evaluate the impact of a QIP targeting both HCPs and patients, based on the KDIGO 2024 recommendations, in individuals with CKD and hyperkalemia. The QIP aims to determine whether implementation of a structured, guideline-based intervention can improve care processes and clinical outcomes in routine practice. The overall study design is illustrated in Fig. 1.

**Fig. 1 Fig1:**
[figure not shown]
Study design

## Study sites and participants

### Site selection

Approximately 50 research centers across China will be selected based on the following criteria: (1) tertiary public hospitals with an established Department of Nephrology, emergency services, and laboratory facilities, and with access to guideline-recommended treatments for hyperkalemia; (2) management of more than 500 non-dialysis patients with CKD and hyperkalemia within the preceding year; (3) demonstrated institutional commitment to improving hyperkalemia management; and (4) preferential inclusion of hospitals with CKD-specific outpatient clinics.

### Participants

Eligible participants must be ≥ 18 years of age at the time of providing written informed consent and be capable of complying with the protocol and informed consent form requirements. Participants must have a diagnosis of CKD with an eGFR > 10 mL/min/1.73 m², calculated using the Chronic Kidney Disease Epidemiology Collaboration (CKD-EPI) 2021 creatinine equation. In addition, a serum potassium level > 5.0 mmol/L documented within 48 h prior to enrollment is required. Exclusion criteria include receipt of dialysis therapy, pseudo-hyperkalemia, acute kidney injury, diabetic ketoacidosis, or cardiac arrhythmias requiring immediate medical intervention. Patients with a history of renal transplantation or those scheduled to undergo renal transplantation will also be excluded. A complete list of inclusion and exclusion criteria is provided in the Supplementary Material.

### Endpoints

Both the KDIGO 2024 and Chinese CKD guidelines recommend the use of RAASi at the maximum tolerated dose to achieve optimal therapeutic benefits, including cardiorenal protection [17–19]. However, in routine clinical practice, RAASi therapy is frequently down-titrated or discontinued in response to hyperkalemia, often in deviation from guideline recommendations. Accordingly, the primary endpoint of this study is designed to capture not only effective potassium control in patients with CKD and hyperkalemia, but also successful RAASi optimization. The primary endpoint is defined as the proportion of patients achieving RAASi optimization while maintaining normokalemia (serum potassium 3.5-5.0 mmol/L) at 48 weeks following implementation of the intervention.

The secondary endpoints include: (1) the proportion of patients with normokalemia (serum potassium 3.5-5.0 mmol/L) at each onsite visit; (2) the proportion of patients achieving RAASi optimization with normokalemia at weeks 12 and 24; (3) the percentage change in urinary albumin-to-creatinine ratio (UACR) from baseline to weeks 48 and 96 among patients receiving RAASi at baseline; (4) the proportion of patients experiencing severe hyperkalemia (serum potassium > 6.5 mmol/L) during the 96-week intervention period; (5) medication possession ratio (MPR) for hyperkalemia therapies, defined as the number of days hyperkalemia medication was used between two onsite visits divided by the total number of days between those visits, assessed at each onsite visit; (6) time to first hyperkalemia recurrence; (7) hospital-level hyperkalemia management status at baseline and at weeks 48 and 96; (8) time to first occurrence of any component of the kidney-specific composite endpoint, defined as sustained eGFR decline ≥ 50%, ESRD, or renal death; (9) eGFR slope over the 96-week follow-up period; (10) time to first occurrence of any component of the heart-specific composite endpoint, including rehospitalization for heart failure (rhHF), worsening heart failure, emergency room visits, or cardiovascular death; (11) time to first occurrence of arrhythmia; (12) frequency of serum potassium testing and number of hyperkalemia episodes during the first 48 weeks of intervention (onsite and remote visits), with hyperkalemia defined as serum potassium > 5.0 mmol/L and multiple measurements within 48 h counted as a single episode; (13) the proportion of patients requiring emergency department visits, emergency dialysis, or hospitalization during the 48-week intervention period; (14) safety and clinical assessments, including adverse events (AEs), serious adverse events (SAEs), adverse drug reactions (ADRs); (15) vital signs; (16) physical examination findings; (17) clinical laboratory parameters; and (18) electrocardiographic assessments.

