### Sample size estimation

The study is expected to enroll approximately 1,000 patients, based on the estimated eligible patient population across China and the participation of approximately 50 research centers over an anticipated enrollment period of 10 months. As this study is descriptive in nature, the sample size was determined to ensure adequate precision of estimates rather than formal hypothesis testing. Assuming that 45% of patients will achieve RAASi optimization while maintaining normokalemia (serum potassium 3.5-5.0 mmol/L) at 48 weeks [20], and allowing for an anticipated 20% dropout rate, a total sample size of 1,000 patients is expected to provide a precision of 3.4% for the primary endpoint, calculated using the normal approximation method.

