### Statistical plans

All statistical analyses will be performed using SAS software (version 9.4 or later). Analyses will be primarily descriptive in nature and will be conducted using non-missing data only.

Except for safety analyses, all efficacy and exploratory analyses will be performed in the full analysis set (FAS), which includes all patients who meet the inclusion and exclusion criteria, unless otherwise specified. Continuous variables will be summarized using the number of observations, mean, standard deviation, median, first and third quartiles, minimum, and maximum. Categorical variables will be summarized as frequencies and percentages. 95% confidence intervals (CIs) will be reported where appropriate. For time-to-event endpoints, analyses will include the number and proportion of patients experiencing each event, along with the corresponding event rates. Kaplan-Meier methods will be used to estimate and graphically present cumulative incidence for both composite and individual endpoints. Changes in eGFR over time will be evaluated using a mixed-effects model for repeated measures (MMRM) to estimate the eGFR slope over the study period.

Safety analyses will be conducted in the safety analysis set (SAS), which includes all patients who have received at least one potassium-binding therapy. The number and proportion of patients experiencing at least one AE, SAE, or ADR will be summarized. Vital signs at each scheduled assessment, as well as findings from physical examinations, electrocardiograms, and laboratory evaluations, will be summarized using descriptive statistics.

A total of four interim analyses are planned, including one primary analysis. The primary analysis is scheduled to occur 48 weeks after enrollment of the final patient.

In addition, predefined subgroup analyses will be performed for the primary and selected secondary endpoints. Subgroups will be defined based on demographic characteristics, baseline disease features (including baseline eGFR to reflect CKD stage), geographic region, and other clinically relevant factors such as history of heart failure, diabetes mellitus, RAASi use, and hyperkalemia treatment patterns.

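### Secondary endpoints (4) and (13) are planned as crude percentages despite anticipated dropout, so they do not estimate the 96-week and 48-week risks

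*Protocol article*

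**What the plan says.** The Endpoints section defines endpoint (4) as "the proportion of patients experiencing severe hyperkalemia (serum potassium > 6.5 mmol/L) during the 96-week intervention period" and endpoint (13) as "the proportion of patients requiring emergency department visits, emergency dialysis, or hospitalization during the 48-week intervention period". In the same list, first recurrence of hyperkalemia (6), the kidney composite (8), the heart composite (10) and arrhythmia (11) are explicitly time-to-event endpoints.

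The Statistical plans section summarizes categorical variables by counts and percentages, takes the full analysis set (FAS, all eligible patients) as the population for everything but safety, and adds: "Analyses will be primarily descriptive in nature and will be conducted using non-missing data only". Event rates and Kaplan-Meier estimates are introduced there for the time-to-event endpoints.

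The Sample size estimation section sets the number of patients while "allowing for an anticipated 20% dropout rate". That figure accompanies the 48-week primary endpoint. No separate figure is given for week 96.

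**The concern.** A proportion of patients with an event during a fixed period is a risk over that period only if everyone is followed to its end or to the event. With planned dropout, some patients leave event-free and their later status is unknown. A crude percentage has to put them somewhere, and the two natural choices err in different ways.

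- **All FAS patients in the denominator.** Dropouts count as event-free to the end. Any event after dropout is missed, so the estimate can only be too low.
- **Event-free dropouts removed as missing.** Dropouts who had an event stay in and those who did not are taken out. If dropout is unrelated to risk, the estimate is too high.

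The article's text points both ways: the FAS suggests the first, the non-missing rule the second.

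The list also treats neighbouring events differently. Recurrence of hyperkalemia is analysed from time to event, but potassium above 6.5 mmol/L is not. Emergency room visits are a time-to-event component of the heart composite, but emergency department visits in (13) are a plain proportion. What is at stake is the absolute level of two harm-related figures that readers will take as period risks.

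**Working it through.** **Inputs from the article.** 1,000 patients, 20% dropout and a 45% primary endpoint rate (Sample size estimation); 95% intervals (Statistical plans); windows of 96 and 48 weeks (Endpoints).

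**Assumptions.** The article gives no expected risk for (4) or (13), so true risks R of 2% to 30% are used. Dropout by week 96 is not given either. Two values are used: 20% in total, and 36%, which is 20% in each 48-week half (1 − 0.8² = 0.36).

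**The plan's own figure.** The article says that "a total sample size of 1,000 patients is expected to provide a precision of 3.4% for the primary endpoint". With 1,000 × 0.8 = 800 patients and a rate of 45%, the half-width is 1.96 × √(0.45 × 0.55 / 800) = 3.45%, which agrees with the stated 3.4%. That figure is not in dispute.

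**Independent dropout.** Let D be the dropout proportion over the window. With constant hazards, put Λ = −ln(1 − R) and Γ = −ln(1 − D), ignoring death.

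- All-FAS proportion: A = Λ / (Λ + Γ) × [1 − (1 − R)(1 − D)]
- Event-free completers: C = (1 − R)(1 − D)
- Event-free dropouts removed: B = A / (A + C)

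R = 10%, D = 20%: Λ = 0.1054, Γ = 0.2231, C = 0.72. A = 0.1054 / 0.3285 × 0.28 = 0.090. B = 0.0898 / 0.8098 = 0.111.

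R = 10%, D = 36%: Γ = 0.4463, C = 0.576. A = 0.1054 / 0.5517 × 0.424 = 0.081. B = 0.0810 / 0.6570 = 0.123.

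R = 30%, D = 20%: Λ = 0.3567, C = 0.56. A = 0.3567 / 0.5798 × 0.44 = 0.271. B = 0.2707 / 0.8307 = 0.326.

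| True risk | Dropout | All FAS | Event-free dropouts removed |
|---|---|---|---|
| 2% | 20% | 1.8% | 2.2% |
| 10% | 20% | 9.0% | 11.1% |
| 30% | 20% | 27.1% | 32.6% |
| 2% | 36% | 1.6% | 2.5% |
| 10% | 36% | 8.1% | 12.3% |
| 30% | 36% | 24.5% | 35.4% |

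Over risks of 2% to 30%, the relative error is about −10% or +9% to +12% at 20% dropout, and about −18% to −19% or +18% to +26% at 36%. Spreading dropout times uniformly gives nearly the same values (9.0% and 11.1% in the second row). A time-to-first-event estimate recovers R in this setting.

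**Dropout related to risk.** Keep the overall true risk at 10%, spread dropout times uniformly, and give dropouts a multiple of the completers' hazard:

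| Hazard ratio, dropouts to completers | 20% dropout: FAS / removed | 36% dropout: FAS / removed |
|---|---|---|
| 0.5 | 9.4% / 11.7% | 8.9% / 13.6% |
| 1 | 9.0% / 11.1% | 8.2% / 12.5% |
| 2 | 8.4% / 10.3% | 7.5% / 11.2% |
| 3 | 8.0% / 9.8% | 7.0% / 10.5% |
| 4 | 7.7% / 9.4% | 6.7% / 10.0% |

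The FAS proportion is below 10% throughout. The other one starts above 10% and, at 20% dropout, falls below it once dropouts have about three times the hazard.

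**Against sampling error.** At 10% and n = 1,000 the 95% half-width is 1.96 × √(0.10 × 0.90 / 1000) = 1.9 points. The errors are 1.0 and 1.1 points at 20% dropout, and 1.9 and 2.3 points at 36%.

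**The case against.** The best defence is that the article is a condensed account, and that denominators and partial follow-up for descriptive secondary endpoints normally belong in the analysis plan, which is not shown. Calling an endpoint a proportion does not forbid estimating it as a cumulative incidence. Nor does the article say that Kaplan-Meier is excluded outside the time-to-event endpoints. This stands in part: silence on the denominator would not by itself be a finding. But the article does assign a summary (percentages) and a missing-data rule, and neither natural denominator under them gives the period risk.

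Other parts stand in full:

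- The upward error is conditional, as the second table shows. A reader might infer that removing event-free dropouts always overstates the risk; nothing in the article says how dropout relates to risk, so that cannot be claimed.
- The two denominators are not the only ones possible. A strict completers-only proportion would be unbiased under independent dropout. It would, however, discard observed events, and with 20% dropout and dropouts at three times the hazard it gives 7.4% for a true 10%.
- Death counts as study completion, so keeping a patient who died event-free as a non-event already matches competing-event handling.
- Potassium is tested at early withdrawal (Table 1, note i). That captures status at exit, but not afterwards.
- Recurrence, the heart composite and arrhythmia already cover part of the harm picture, though none isolates potassium above 6.5 mmol/L or all hospitalization.

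**Conclusion.** The point holds at modest priority. As described, (4) and (13) are crude percentages under anticipated loss to follow-up. The FAS version is too low under any dropout mechanism unless no dropout would later have had an event. The version without event-free dropouts is too high under independent dropout only.

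The sizes are illustrative. They rest on assumed true risks, constant hazards and, for week 96, an assumed dropout. A reader might take 8.1% against 12.3% as following from the plan's own figures. It does not: the article states one dropout figure, 20%, in its 48-week calculation. With 20% in total, a 10% risk becomes 9.0% or 11.1%, and each error is smaller than the sampling half-width. A reader might also conclude that the denominator outweighs sampling error. At 36% dropout the two denominators differ by 12.3 − 8.1 = 4.2 points, but each is only about one half-width from the truth.

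It would also go too far to call these the trial's main safety outcomes. The article lists safety assessments separately at (14) to (18), and no test, comparison or sample size depends on (4) or (13).

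**What to change.** Estimate (4) and (13) as cumulative incidence at week 96 and week 48 from the date of first event, with 95% confidence intervals. Censor at last contact, or for potassium at the last potassium measurement. Treat death as a competing event, because a Kaplan-Meier estimate that censors deaths would overstate the risk. Keep the crude counts as description, with the denominator stated.

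State two limits alongside the estimate. It assumes non-informative dropout, so it does not cure dropout related to risk. And severe hyperkalemia is known only when potassium is tested, so event times are approximate; scheduled onsite visits are 12 to 24 weeks apart.

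The cost is analysis wording and programming. Endpoints (6), (8), (10) and (11) already need event dates, and emergency visits, emergency dialysis and hospitalization are collected under the same clinical-events item as the composites (Table 1, note o), so little or no new data collection should be needed.
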